#### Clinical Significance and Statistical Reliability

Meaningful or clinically significant changes occur when an individual is in the dysfunctional (clinical) range at the commencement of treatment and in the functional (nonclinical) range at the end of treatment [61,62]. The clinical significance index (CSI) indicates whether individuals have made meaningful improvements to their emotional health and moved from being clinically dysfunctional to functional [63]. The reliable change index (RCI) verifies the statistical significance of any change in an individual’s score from pre- to postintervention [62]. This approach is particularly useful for single-case designs because it allows researchers to focus on individual functioning [64] and to adjust treatment if necessary. Jacobson and Truax [62] developed a classification system to describe the change in a participant’s mental health in a study’s conclusion: *recovered*=clinically significant and statistically reliable; *improved*=not clinically significant, but statistically reliable; *unchanged*=not clinically significant or statistically reliable; and *deteriorated*=clinically significant and/or statistically reliable in a worsening direction.

To determine the CSI, a cutoff point between the scores obtained by the functional and dysfunctional populations on a particular measure is identified [61,62]. Scores on either side of this point are statistically more likely to indicate whether an individual is functional or dysfunctional [61,62]. Normative data are required for both functional and dysfunctional populations for the measures being used. The CSI is based on the following formula [62]:

where 1 represents the nonclinical population and 2 represents the clinical population.

The RCI is a function of a measure’s standard deviation and reliability [61]. It measures an individual’s change in self-reported score from pretreatment to follow-up for statistical reliability. If an individual’s change exceeds 1.96 times the SE, the change is statistically reliable at *P*<.05 because it is unlikely to occur more than 5% of the time as a result of measure discrepancy or chance [61]. The RCI is calculated as follows [62]:

where S_diff_=√2(S_E_)^2^ and S_E_=*SD* of both groups×(√1−test-retest reliability).

Clinical significance will be calculated based on participants’ scores on the mental health and well-being outcome measures (DASS-21 and OQ-45.2) across the various phases using the framework suggested by Jacobson and Truax [62]. Using the OQ-Analyst platform, clinical significance will be compared with statistical significance and visual inspection.

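### 'Deteriorated' can be assigned without reliable change, unlike 'recovered' and 'improved', so measurement error near a cutoff is labelled deterioration and the mirror-image crossing has no class

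*Protocol article*

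**What the plan says.** The protocol article, section Clinical Significance and Statistical Reliability, sorts each participant by two criteria: crossing a cutoff between the functional and dysfunctional ranges (clinical significance) and the reliable change index (statistical reliability). The four classes are worded as follows.

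- *Recovered* needs both criteria: "clinically significant and statistically reliable".
- *Improved* needs reliable change without a cutoff crossing: "not clinically significant, but statistically reliable".
- *Unchanged* reads "not clinically significant or statistically reliable; and" (the last word leads on to the fourth class).
- *Deteriorated* accepts either criterion: "clinically significant and/or statistically reliable in a worsening direction".

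On reliability the text says: "If an individual’s change exceeds 1.96 times the SE, the change is statistically reliable at" the .05 level. The reason it offers is a chance rate of no more than 5% for a change that reflects measurement error alone. The terms of the index follow: "where S_diff_=√2(S_E_)^2^ and S_E_=*SD* of both groups×(√1−test-retest reliability").

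The section Mental Health and Well-Being gives the OQ-45.2 a total-score cutoff of 63 or more and a test-retest reliability of .84. The classification is to be applied to the DASS-21 and the OQ-45.2. The section Study Design expects about 3 to 5 participants per app to supply enough data after attrition.

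**The concern.** Both favourable classes need reliable change. The unfavourable class accepts either criterion alone, so a one-point move over the cutoff in the worse direction is labelled deterioration, although a one-point difference is well inside measurement error.

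The opposite move also has a problem. A change from 63 to 62 crosses the cutoff but is not reliable. It is not recovered (not reliable), not improved (again not reliable) and not unchanged if that class means that neither criterion is met. If unchanged is instead read as failing at least one criterion, it overlaps with improved. Under neither reading are the four classes both exhaustive and mutually exclusive.

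At stake is the individual outcome label. Few completers are expected per app, and the plan rests generalisation on results being comparable from case to case, so one spurious deterioration could change what is said about an app.

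**Working it through.** **Inputs from the protocol article.** Test-retest reliability r = .84 and cutoff 63 for the OQ-45.2 (Mental Health and Well-Being). S_E = SD × √(1 − r), S_diff = √(2 × S_E²), multiplier 1.96 and stated chance rate 5% (Clinical Significance and Statistical Reliability). Completers per app: 3 to 5 (Study Design).

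**Assumptions.** Normal measurement error that is independent at the two occasions, and no true change. The SD is not given, so 15, 20 and 25 points are used for illustration. It matters only for translating S_E into points.

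**Step 1: the plan's own 5%.** For a stable person, post minus pre has standard deviation S_diff = √2 × S_E. The chance of exceeding 1.96 × S_diff in either direction is 2 × (1 − Φ(1.96)) = 0.0500, which reproduces the stated 5%. In the worsening direction alone it is 2.5%.

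**Step 2: scale on the OQ-45.2.** S_E = SD × √(1 − .84) = 0.400 SD, and 1.96 × S_diff = 1.96 × √2 × 0.400 SD = 1.109 SD.

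| Assumed SD | S_E | Reliable-change threshold |
|---|---|---|
| 15 | 6 | 16.6 points |
| 20 | 8 | 22.2 points |
| 25 | 10 | 27.7 points |

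A move from 62 to 63 is 1 point.

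**Step 3: false deteriorated labels.** Let the true score lie d × S_E on the functional side of the cutoff. The chance of an upward crossing (functional before, dysfunctional after) is Φ(d) × (1 − Φ(d)). At d = 0 this is 0.5 × 0.5 = 25%. At d = 1 it is 0.841 × 0.159 = 13.3%. At d = 2 it is 0.977 × 0.023 = 2.2%. The label as written is assigned with probability P(crossing) + P(reliable worsening) − P(both). The overlap was obtained by simulation (4 million pairs).

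| d | Crossing | Reliable worsening | Both | As written (either) | Crossing, not reliable |
|---|---|---|---|---|---|
| 0 | 25.0% | 2.5% | 2.4% | 25.0% | 22.6% |
| 0.5 | 21.3% | 2.5% | 2.3% | 21.5% | 19.0% |
| 1 | 13.3% | 2.5% | 2.0% | 13.8% | 11.3% |
| 1.5 | 6.2% | 2.5% | 1.4% | 7.3% | 4.8% |
| 2 | 2.2% | 2.5% | 0.8% | 3.9% | 1.4% |
| 3 | 0.1% | 2.5% | 0.1% | 2.5% | 0.0% |

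The last column is the excess due to the and/or wording. The two occasions are exchangeable when nothing has changed, so it is also the chance of an unreliable crossing in the better direction, which has no class.

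**Step 4: per app (illustrative).** Suppose every completer is stable and sits at d = 1 on one measure. The chance of at least one false deteriorated label is:

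- 3 completers: 1 − 0.862³ = 36%, against 1 − 0.975³ = 7% if reliability is required;
- 4 completers: 1 − 0.862⁴ = 45%, against 10%;
- 5 completers: 1 − 0.862⁵ = 52%, against 12%.

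**The case against.** **The size depends on where people start.** A participant already on the dysfunctional side of a measure at the pretreatment assessment cannot be labelled deteriorated by crossing into it. Entry requires diagnosed mild-to-moderate anxiety and/or depression, and no OQ-45.2 entry score places people just below 63. This stands: the documents do not show how many participants lie in the affected band, and stable participants in general are not misclassified. The band need not be empty, because a participant with only one of the two conditions may start in the functional range of the other DASS-21 subscale.

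**It cannot flatter the apps.** Research question 1 and the hypothesis concern improvement, and both favourable classes require reliable change. This also stands. A reader might infer that the answer to research question 1 is invalidated, but the and/or wording creates no false recovery or improvement. Its error runs against the apps.

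**The classification is not the only evidence.** Time series analysis of the daily distress ratings and visual inspection sit beside it. True, but they do not correct a label on the DASS-21 or OQ-45.2.

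**A tempting stronger reading concerns the threshold.** Since the text says "change exceeds 1.96 times the SE, the change is statistically reliable" and defines S_E shortly afterwards, a reader might infer that the plan uses the single-score standard error. That would give a two-sided chance rate of 2 × (1 − Φ(1.96/√2)) = 16.6%. The document does not support this. The legend to the index defines S_diff, which has no purpose unless it is the denominator, and the stated 5% is reproduced with S_diff and not with S_E. 'The SE' is loose wording for the standard error of the difference.

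**Numeric thresholds for each measure** are not printed, but a journal article may leave these to the full plan, so their absence is no fault.

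**Conclusion.** The point holds in limited form. As printed, deteriorated does not require reliable change, and an unreliable crossing in the better direction has no class. For a stable participant the false deteriorated rate is about 25% with the true score at the cutoff, 14% at one S_E and 4% at two S_E on the functional side, against 2.5% under a reliability requirement. By three S_E there is no excess.

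These rates rest on normal, independent measurement error and no true change. In S_E units they depend neither on the SD nor on the exact cutoff, so they apply equally if the cutoff calculated from normative data differs from 63. How many participants are affected cannot be determined from the document. The consequence is overstated deterioration, which matters mainly because 3 to 5 cases per app leave little room for one wrong label. The threshold sentence needs clarification and is not an error in the rule.

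**What to change.** Make these changes in Clinical Significance and Statistical Reliability before outcome data are classified:

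1. Define *deteriorated* as statistically reliable change in the worsening direction.
2. Define *unchanged* as no statistically reliable change, whether or not the cutoff is crossed. Unreliable crossings in either direction may be reported separately as a descriptive count.
3. As a clarification only, replace '1.96 times the SE' with '1.96 times S_diff'.

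With the first two changes the four classes are exhaustive and do not overlap. The cost is three edits in one section, with no new data or measures and no change to sample size. The edits concern the analysis label only and leave the welfare-contact and removal criteria as they are.

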#### Visual Inspection

Visual inspection of plotted data allows for a personal judgment about the effect of an intervention and can often produce more meaningful information than approaches involving the calculation of statistical significance [20]. In this study, visual inspection will be possible using up to 112 data points of SUDS ratings, as illustrated in Figure 3. Data obtained from the uMARS will be plotted against participant ratings from the mental health and well-being outcome measures (DASS-21 and OQ-45.2) and SUDS data and inspected for any observed relationships.

**Figure 3 figure3:**
[figure not shown]
Example of how participant data may be affected and graphed using a multiple baseline across-individuals design.

#### Data Management

Management and storage of data will occur in line with the Management and Storage of Research Data and Materials Policy of the University of New England [65]. Specifically, all nondigital materials will be scanned and digitally stored indefinitely with all other digital information pertaining to this research on the University of New England research data cloud storage facility. Digital information will be password protected and accessible only to appropriate research staff.

#### Data Exclusion

Data will be excluded from time series and visual analyses if a participant fails to provide a minimum of 20 SUDS ratings in phase 1 (baseline) and/or phase 4 (postintervention) and 40 SUDS ratings in phase 3 (intervention). Data will be excluded from CSI and RCI analyses if a participant fails to complete baseline and/or postintervention mental health and well-being outcome measures (DASS-21 and OQ-45.2). Owing to the nature of the proposed study design, participants who dropout because they did not provide the required minimum data cannot be replaced by new participants once the baseline phase has commenced.

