**Methods:**

A multiple baseline across-individuals design will be employed. A total of 50 participants will be recruited (10 for each app) who will provide baseline data for 20 days. The sequential introduction of an intervention phase will commence once baseline readings have indicated stability in the measures of participants’ mental health and will proceed for 10 weeks. Postintervention measurements will continue for a further 20 days. Participants will be required to provide daily subjective units of distress (SUDS) ratings via SMS text messages and will complete other measures at 5 different time points, including at 6-month follow-up. SUDS data will be examined via a time series analysis across the experimental phases. Individual analyses of outcome measures will be conducted to detect clinically significant changes in symptoms using the statistical approach proposed by Jacobson and Truax. Participants will rate their app on several domains at the end of the intervention.

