## Methods

### Study Design

This study is registered with the Australian and New Zealand Clinical Trials Registry (ANZCTR), which is a primary registry in the World Health Organization Registry Network (registration number: ACTRN12619001302145p).

A multiple baseline across-individuals design will be employed. Multiple baseline designs in mental health intervention studies are those where a baseline period of stability of symptoms is established before the intervention is introduced. In this way, each participant acts as their own control, and internal validity is demonstrated when there is no change in symptoms until after the treatment is introduced [18]. In the design to be used in this study, all participants commence the baseline period at the same time but start the treatment at different times after a minimum number of daily data readings (at least 20) have been received. This sequential commencement approach further strengthens the internal validity by reducing the likelihood of history, maturation, or other extraneous factors explaining any observed emotional or behavioral change that occurs simultaneously with the introduction of the treatment. The multiple data recordings allow for the use of analytical techniques such as a time series analysis [20,26] and will involve participants reporting ratings of subjective units of distress (SUDS) via SMS text messaging using a 10-point scale. In this design, 4 or more baselines are recommended [18,20], and these will follow the pattern shown in Figure 1.

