#### Phase 2 (Baseline)

Accepted participants provide daily SUDS ratings for a minimum of 20 days or until a stable baseline profile of current psychological distress is achieved. At the end of this phase, the mental health and well-being outcome measures (DASS-21 and OQ-45.2) are completed.

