#### Phase 4 (Postintervention)

Participants provide SUDS ratings for at least 20 days following the completion of their official intervention period. Once a minimum of 20 SUDS ratings have been received, they will complete another DASS-21 and OQ-45.2. Participants are given information on all the apps so that they may explore the others if they wish.

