#### Time Series Analysis

A process for conducting time series analyses for psychological research was described by Borckardt et al [59] using the *R* statistical software package. In the proposed study, the commencement of the intervention will be the predictor in a regression model that uses data before and after this point to determine if there has been a statistically significant impact on subjective distress, as measured by SUDS ratings. A minimum of 20 data points are required in each phase [20,26]. The *R* statistical package will use conventions of autoregressive integrative moving average (ARIMA) modeling to account for autocorrelated data [60] when building the model.

The time series analyses [59] will evaluate statistically significant changes across the phases of the proposed study. Overall level and trends across time will be considered, and if necessary, adjustments will be made for irregular variation effects. An *irregular factor* is similar to the error terms used in many statistical models, such as generalized linear modeling. The methods of making such adjustments differ depending on the nature of the collected data but may include the augmented Dickey-Fuller test, Durbin-Watson test and/or the Ljung-Box test as part of an ARIMA model.

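### Missing the SUDS minimum in one phase drops a participant from every time series and visual analysis, including the baseline-versus-intervention comparison, which needs no postintervention ratings

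*Protocol article*

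**What the plan says.** **The rule.** Data Exclusion states: "Data will be excluded from time series and visual analyses if a participant fails to provide a minimum of 20 SUDS ratings" in the baseline phase "and/or phase 4 (postintervention) and 40 SUDS ratings in phase 3 (intervention"). The removal criteria in the eligibility textbox use the same three minimums (20, 20 and 40). Neither place keeps the phases that are complete.

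**The analysis.** Time Series Analysis makes the start of the intervention the predictor in a regression on ratings before and after that point. It adds: "A minimum of 20 data points are required in each phase".

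**Phase length.** The statements differ.
- The abstract gives a flat 20 days for each short phase: "who will provide baseline data for 20 days" and "Postintervention measurements will continue for a further 20 days".
- Study Design speaks of a postintervention minimum of 3 weeks. Visual Inspection gives a maximum of 112 ratings, and Limitations and Strengths speaks of 16 weeks.
- Study Design also says participants "start the treatment at different times after a minimum number of daily data readings (at least 20) have been received". Phase 2 says "Accepted participants provide daily SUDS ratings for a minimum of 20 days or until a stable baseline profile" is reached. Phase 4 says "Participants provide SUDS ratings for at least 20 days following the completion of their official intervention period", with the questionnaires following once 20 ratings have arrived.

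**The target.** Study Design plans 10 participants per app and expects about 3 to 5 with enough data after 50% to 60% attrition.

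**The concern.** The regression asks whether distress changed when the app was introduced. That needs a baseline and an intervention series. Postintervention ratings answer a different question, whether the change lasted. A single rule covering all three phases makes the first question depend on data collected for the second.

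Two things are at stake. First, cases: with so few per app, one or two lost series can decide whether an app has the replications the design relies on, and dropouts cannot be replaced once baseline has begun. Second, selection: a postintervention minimum keeps only people who were still replying after treatment had begun and ended. If those for whom an app did little are likelier to stop replying, the reported cases will look too favourable. The same exclusion applies to the plots, where partial series are informative and no model requirement is involved.

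**Working it through.** **1. The plan's own figures.** Completers per app = 10 × (1 − attrition): 10 × 0.50 = 5 and 10 × 0.40 = 4. This agrees broadly with 3 to 5, although 3 would need 70% attrition. The maximum of 112 ratings equals 21 + 70 + 21 days, or 16 × 7. The abstract's lengths give 20 + 70 + 20 = 110. The 112 figure therefore implies 21-day short phases.

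**2. Share of days that must be answered.** Short phases: 20/20 = 100% (abstract), 20/21 = 95% (3 weeks), 20/28 = 71% (if run to four weeks). Intervention: 40/70 = 57%.

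**3. Chance that a completer meets the minimums.** The article gives no daily reply probability p, so p is an assumption, with days taken as independent. For a short phase of L days, b = P(X ≥ 20) with X ~ Binomial(L, p). For the intervention phase, P(X ≥ 40) with X ~ Binomial(70, p) is about 1 at each p used. The present rule therefore passes with probability b². A per-contrast rule for baseline versus intervention passes with probability b.

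Example, L = 21 and p = 0.90: b = 0.9^21 + 21 × 0.9^20 × 0.1 = 0.109 + 0.255 = 0.365; b² = 0.133.

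| L (days) | p | Present rule, b² | Per contrast, b |
|---|---|---|---|
| 20 | 0.90 | 1.5% | 12.2% |
| 20 | 0.95 | 12.9% | 35.8% |
| 21 | 0.90 | 13.3% | 36.5% |
| 21 | 0.95 | 51.4% | 71.7% |
| 28 | 0.80 | 82.8% | 91.0% |
| 28 | 0.90 | 99.8% | 99.9% |

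**4. Lost only through postintervention.** This is b × (1 − b). With 21-day phases it is 23.2% of completers at p = 0.90 and 20.3% at p = 0.95. With 28-day phases it is 8.2% at p = 0.80 and 0.1% at p = 0.90.

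**5. In cases.** Of 5 completers with 21-day phases and p = 0.95, the expected usable number rises from 5 × 0.514 = 2.57 to 5 × 0.717 = 3.58. The chance of at least 3 usable rises from 52.6% to 85.9%.

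**6. If a short phase stays open until 20 ratings arrive.** Its mean length is 20/p: 25.0, 22.2 and 21.1 days at p = 0.80, 0.90 and 0.95. Anyone who keeps replying then meets the minimum. The rule costs only those who stop.

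**7. A hint at p.** The expected average reimbursement of Aus $45 at Aus $0.50 per rating implies 90 ratings, and 90/112 = 80%. That average may include dropouts, so it is not an estimate of p among completers.

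**The case against.** The strongest reply is that the operative procedure lets missed days be made up. Study Design and Phases 2 and 4 set 20 days or 20 ratings as minimums without a cap, so a reader who infers that the rule demands almost perfect compliance would be relying on the condensed abstract or on the 112-rating maximum. The stagger also gives participants in later positions longer baselines, so squaring one short-phase probability is too pessimistic for them. Both objections stand: the 20- and 21-day rows hold only if phases are fixed.

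Two other stronger readings fail.
- A reader might see the 40-rating intervention minimum as contradicting the 20 in Time Series Analysis. That section states a floor, and a stricter floor for a 70-day phase is compatible with it.
- A reader might add this loss to the 50% to 60% attrition. Data Exclusion itself counts people with too few ratings as dropouts, and Study Design describes the 3 to 5 as having enough data, so the two may overlap.

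It can also be said that each participant is their own control, so exclusion changes which cases are reported rather than the estimate within a case, and that no passage links missed replies to how well an app worked. That is fair. The selection is a risk, not a demonstrated bias.

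Finally, the exclusion is not beyond doubt in wording. Data Exclusion joins the short-phase and intervention minimums with *and*, so read literally it excludes only someone who misses both. The removal criteria join them with *or*. The natural reading is that any shortfall excludes, but the text should say so.

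None of this answers the central point: nothing in the article retains a complete baseline and intervention series when postintervention ratings fall short.

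**Conclusion.** The concern holds for the all-or-nothing structure of the rule. On its natural reading, it discards baseline-versus-intervention series that the stated regression could use, and removes the same people from the plots.

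The size cannot be fixed from the article. With fixed 21-day short phases, per-contrast use adds about 20 to 23 percentage points to a completer's chance of being usable at reply rates of 90% to 95%. With short phases that can run to 28 days, the gain is about 8 points at 80% reply and negligible at 90%; it then mainly concerns people who stop during postintervention. These figures rest on assumed reply rates and independent days.

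The change is worth making under either reading, because the design depends on a handful of cases per app and cannot replace those lost. The documents do not support a claim that near-perfect compliance is required throughout.

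**What to change.** 1. In Data Exclusion, apply the minimums per contrast. Baseline versus intervention needs the minimums in those two phases only, and intervention versus postintervention likewise. The 40-rating intervention minimum can stay.
2. Plot every participant's available ratings in the visual analysis, marking incomplete phases.
3. Report participants who meet all three minimums as a sensitivity analysis.
4. Reconcile the lengths of the short phases across the abstract, Study Design, Phases 2 and 4 and the 112-rating maximum, and state whether a phase has a cap.
5. Align the conjunctions in Data Exclusion with those in the removal criteria. Correct the phase label as well: Data Exclusion calls baseline phase 1, while Procedure makes it Phase 2.
6. In the removal criteria, say how data already collected are used after removal. This concerns the data only, not when a participant is removed.

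The cost is a different participant count for each contrast, which must be reported, and the matching edit to the removal criteria. Under Ethics Approval, any change to procedures goes to the ethics committee and is noted on the trial registration. No additional data collection is needed.
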